## 2. Methods

### 2.1. Study Design, Setting and Aim

This multicenter, prospective, observational study will evaluate the safety of TEA in clinical practice. The study protocol is registered with the Clinical Research Information Service (CRIS; https://cris.nih.go.kr, (accessed on 16 December 2024); registration number KCT0008912). Participants will be recruited from three university-affiliated hospitals and two traditional Korean medicine clinics in Korea. Patients receiving at least one TEA treatment in a real-world setting, in line with the eligibility criteria, will be enrolled, and all AEs occurring in participants for a total of 3 months will be prospectively collected. In clinical practice, each patient will receive an appropriate number of TEA treatments based on their disease and condition; therefore, all additional TEA treatments after the first treatment will be collected as V2 to Vn in this study. Data regarding all TEAs received by participants and all AEs occurring during the study period will be collected and evaluated. The study procedure and assessment protocol for this trial are presented in Figure 1 and Table 1.

This study aimed to prospectively evaluate and validate the safety of TEA in real-world clinical practice. This observational approach enables the collection of safety data from a diverse patient population to reflect the complexities of actual clinical practice.

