#### 2.5.2. Statistical Methods

The analysis group will include participants who have received at least one TEA treatment. The main observation indicators, including the incidence rate of AEs and the treatment discontinuation rate, will be collected and analyzed without replacing the missing data. Continuous data will be represented using descriptive statistics, such as the number of participants, mean, and standard deviation, whereas categorical data will be presented as frequencies (N) or ratios (%). When necessary, a 95% confidence interval will be calculated. Unless otherwise specified, the statistical tests will be conducted using a two-sided significance level of 5%.

Student’s *t*-test will be used to compare normally distributed continuous variables and the Wilcoxon rank-sum test or Mann–Whitney U test will be used to compare non-parametric continuous variables between the patient groups with AEs and those without. A Shapiro–Wilk test and Kolmogorov–Smirnov test will be used to assess the normality of the distribution. The chi-square test (or Fisher’s exact test, when appropriate) will be used to compare dichotomous variables such as sex, the presence of comorbidities, and co-medications between the patient groups with and without AEs. Variables with *p* < 0.05 in the bivariate analysis or those considered clinically relevant will be included in the final regression model. The Kaplan–Meier method will be used to analyze the incidence of AEs and Cox proportional hazards regression will be used to analyze the differences in the incidence of AEs between subgroups including demographic characteristics, TEA materials or procedures.

All AEs collected in the study will be categorized according to the SOC and PT as defined in the MedDRA. The incidence and incidence rates will be presented by PT; however, multiple occurrences of the same AE by PT in the same subject will be considered as a single event. Furthermore, different discovered severities and causalities for the same AE will be treated as the maximum severities and causalities, respectively. Moreover, AEs associated with TEA and SAEs will be presented as events.

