By enrolling a large and diverse patient population across multiple centers, we aim to capture a comprehensive range of AEs and their potential correlations with different treatment parameters. Detailed documentation of each TEA procedure, including the type of threads, insertion techniques, and treatment areas, allows for a thorough analysis of factors that might influence the occurrence of AEs. Additionally, this study aims to evaluate safety with follow-up periods extending up to 3 months post-treatment. In our preliminary pilot study, most AEs occurred within the first 14 days, most often on the day of the procedure, and resolved spontaneously without any medical treatment. Furthermore, no additional AEs were observed after 3 months, suggesting that AEs were concentrated early on [45]. In addition, previous systematic reviews have reported that AEs following TEA were predominantly local reactions, most of which were mild, transient, and occurred in the acute post-treatment period [28,38]. This approach allows for the capture of both immediate and delayed AEs, contributing to a more comprehensive safety profile of TEA. Our systematic approach to data collection and analysis aims to contribute to improving evaluations in traditional East Asian medical practices. The systematic recording of treatment details and AEs can be applied to acupuncture, moxibustion, and herbal medicine studies.

For practitioners, understanding the risk profiles associated with different TEA techniques and materials can guide safer practice and improve patient outcomes. For patients, transparent safety information can help with making informed decisions regarding their treatment options. For researchers, the data will provide a foundation for further investigations into the mechanisms underlying AEs and the development of strategies to mitigate risks. Additionally, regulatory bodies and policymakers can use the findings to establish guidelines and standards for the safe practice of TEA and similar other interventions.

In conclusion, this study aims to contribute to the body of knowledge regarding the safety of TEA by providing systematic and comprehensive safety data. The data generated in this trial will serve as a foundation for further investigation and the development of evidence-based clinical guidelines.

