## Figures and Tables

**Figure 1 healthcare-13-00135-f001:**
[figure not shown]
Flowchart of the observational study. Abbreviations 7D, 1M, and 3M represent 7 days, 1 month, and 3 months after TEA treatment, respectively.

**Table 1 healthcare-13-00135-t001:** Schedule of observations. The ● indicates at which point of the trial the respective assessments will take place. Vn represents additional treatments administered within the 3-month observation period. In such cases, follow-up assessments are conducted 7 days after each additional treatment to monitor any adverse events. Continuous self-reporting means that during the 3-month follow-up period, patients are encouraged to report any adverse events at any time using an app or diary.

	Screening	Registration		Observation Period				
Time Point	Screening Visit (V0)	Baseline (V1)	Additional Treatments (Vn)	One Week Post-Treatment (V1+7D)	One Week Post-Additional Treatment (Vn+7D)	One Month Post-Treatment (V1+1M)	Three Months Post-Treatment (V1+3M)	Continuous Self-Reporting

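### Intervention factors are analysed per patient although the number of TEA sessions varies, so contrasts between materials or techniques can partly reflect course length

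*Protocol article*

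**What the plan says.** Section 2.1 makes the amount of treatment a clinical choice: "each patient will receive an appropriate number of TEA treatments based on their disease and condition", and "all additional TEA treatments after the first treatment will be collected as V2 to Vn in this study". Table 1 has target disease, product, thread type, area, insertions, thread and needle specifications and depth recorded at V1 and again at each Vn. Its legend adds that "follow-up assessments are conducted 7 days after each additional treatment to monitor any adverse events".

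The analysis in section 2.5.2 takes the patient as its unit. Bivariate tests are made "between the patient groups with AEs and those without". For incidence, "The Kaplan–Meier method will be used to analyze the incidence of AEs". For risk factors, "Cox proportional hazards regression will be used to analyze the differences in the incidence of AEs between subgroups", and the subgroups named include TEA materials or procedures. In the tables by preferred term, "multiple occurrences of the same AE by PT in the same subject will be considered as a single event". Variables enter the final model if the bivariate p is below 0.05 or if they are thought clinically relevant. Number of sessions is named neither there nor among the intervention factors in section 2.4.1.

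**The concern.** A patient with several sessions has several occasions for an AE and several extra 7-day checks. A patient with one session has one. The Discussion reports that in the pilot "most AEs occurred within the first 14 days, most often on the day of the procedure", so risk follows each procedure and recurs at every Vn.

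If one thread type or technique is used mainly for conditions that need longer courses, its users will show more AEs per patient even when each session is equally safe. This is plausible, because the Introduction says that materials and protocols differ across applications, and section 2.1 ties session number to disease. In addition, a material that changes between sessions has no defined value in a patient-level subgroup.

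How intervention factors influence AEs is a stated aim (sections 1 and 2.4.3), and the Discussion expects the results to guide technique, choice of material, guidelines and policy. A product could be labelled riskier because it is used more often per patient.

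**Working it through.** **The plan's own figure.** Section 2.5.1: n* = 0.12 × 0.88 × 1.96² / 0.035² = 331.16, and 331.16 / 0.95 = 348.6, so 349. It reproduces. It concerns one proportion among participants and is not affected by this point.

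**What 12% implies per session.** The article does not say whether 12% is per patient or per session. If it is per patient, the per-session risk is 1 − 0.88^(1/k) for k sessions: 12% (k = 1), 6.2% (2), 3.2% (4), 2.1% (6). An assumed 4% to 5% per session lies within this range.

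**Per-patient risk at equal per-session risk p.** Risk = 1 − (1 − p)^k. At p = 5% this gives 5.0% (k = 1), 9.8% (2), 18.5% (4) and 26.5% (6). The cumulative hazard is −k·ln(1 − p). For two materials with fixed counts, the cumulative hazard ratio at the end of treatment is therefore exactly k_B / k_A, although the true per-session ratio is 1.

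**Simulated Cox model for time to first AE, material as sole covariate.** Assumptions: 332 evaluable patients, two materials 1:1, weekly sessions, onset on average 2 days after a session, censoring at day 90, 2,000 runs. Each cell gives the median hazard ratio and the share of runs with p < 0.05.

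| Sessions, A vs B | p = 3% | p = 5% | p = 12% |
|---|---|---|---|
| 2 vs 2 | 0.99, 4.1% | 0.98, 3.2% | 1.00, 4.7% |
| 1 vs 2 | 2.02, 19.9% | 2.04, 34.5% | 1.94, 65.0% |
| 2 vs 4 | 1.94, 37.4% | 1.94, 57.8% | 1.87, 86.9% |
| 2 vs 6 | 2.90, 86.8% | 2.87, 96.5% | 2.62, 100% |
| 1 vs 4 | 4.01, 84.3% | 3.88, 97.3% | 3.74, 100% |

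**Overlapping counts.** The table separates the materials completely, which is an extreme case. With counts that overlap (assumed distributions, 4% to 5% risk per session), averages of 2.1 versus 2.5 gave a hazard ratio of about 1.2 with about 6% rejection. Averages of 2.1 versus 3.0 gave about 1.4 with 14% to 19% rejection. The ratios of mean counts agree: 2.5 / 2.1 = 1.19 and 3.0 / 2.1 = 1.43.

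**Session as the unit.** With events divided by sessions and variance clustered on patient (p = 3% to 12%; 1 vs 2, 1 vs 4, 2 vs 4 and 2 vs 6 sessions; with and without differences in risk between patients), the median risk ratio was 0.99 to 1.02 and rejection 2.9% to 5.5%. These runs had no stopping because of AEs.

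**Adjusting for sessions received.** A Cox model with the final count as a fixed covariate was simulated with 5% risk, averages of about 2 versus 4 sessions and 14-day spacing. The hazard ratio was 1.01 with no AE-related stopping, 1.46 if 10% of AE patients stop, 2.11 if 20% stop and 5.9 if 50% stop. The true ratio is 1 and all stopping rates are assumed.

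**The case against.** The strongest reply is that the bias needs a link between material and course length, and the article states none. Its only figure on session numbers is the cited retrospective facial palsy study in the Introduction: more than 200 treatments in 82 patients, or about 200 / 82 = 2.4 each. With modest, overlapping differences the distortion can be negligible. This stands, and the size must be given as a range that starts at nil.

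Second, number of sessions could enter the model as clinically relevant. That route is open but unsafe as a fixed covariate. Section 2.4.3 makes discontinuation due to AEs an outcome, so the final count can be a consequence of AEs.

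A reader might go further in four ways that the documents do not support.

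- **That longer-course materials will look harmful.** This is conditional on the unstated link.
- **That the comparison of patients with and without AEs is reverse-causal for treatment quantity.** Section 2.5.2 names no comparison of session counts. Section 2.4.1 lists the intervention factors among data taken at the start of the study.
- **That procedure-day peaks invalidate proportional hazards.** Cox regression leaves the baseline hazard free, ties are routinely handled, and no time origin is stated. Only schedules that differ between groups matter.
- **That the headline incidence is wrong.** Risk per patient over three months is a legitimate measure and is what the sample size addresses. Counting once per preferred term is a common convention for safety tables. The same paragraph also promises event presentations for TEA-associated AEs and SAEs, though without a session denominator.

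An unseen analysis plan may refine the models, but the patient-level approach to materials and procedures is stated in the article itself.

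**Conclusion.** The point holds as a conditional bias in the analysis of intervention factors. As written, a contrast between materials or procedures mixes risk per session with number of sessions whenever the two are associated. With equal per-session risk of 4% to 5%, the spurious hazard ratio runs from 1.0 (equal counts), through about 1.2 to 1.4 (overlapping counts averaging 2.1 versus 2.5 to 3.0), to about 2 to 3 (2 versus 4 or 2 versus 6 sessions). Per-session risk, spacing, onset and session distributions are all assumptions. The documents give no session distribution and no material-by-course association, so the real size is unknown. The plan should be changed, but this is a fault in a secondary analysis and does not touch the main incidence result.

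**What to change.** Keep the patient-level 3-month incidence as the main descriptive measure and add AEs per 100 TEA sessions, counting every occurrence.

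For intervention factors, use one record per session with exposures as recorded at that session. Fit a GEE or mixed model clustered on participant, with session number (its order in the course) as a covariate. A Cox model with exposures updated at each Vn is an acceptable alternative.

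Assign each AE by onset date to the most recent session or, for local AEs, to the most recent session that treated that area. Follow each session until the next one or until 3 months, so that AEs starting after day 7 are kept, because the study aims to capture delayed AEs. Use the 7-day window, which the V1+7D and Vn+7D checks cover, as a sensitivity analysis. Do not adjust for the final number of sessions received.

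The cost is analysis-plan wording, a session-level dataset and slightly more analysis work. Table 1 already collects the exposures and onset dates. The price is some ambiguity in attributing late AEs to a session, and follow-up of unequal length between sessions in the main version of the model.

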#### 2.4.3. Outcome Measures

The development of a standardized AE-reporting form is essential to facilitate accurate data collection, improve the quality of post-medical treatment, and ensure patient safety. The Medical Dictionary for Regulatory Activities (MedDRA) is a standardized international lexicon that is used by regulatory authorities for data related to medical treatments [35]. In the present study, the safety information report was developed based on the integration of MedDRA system organ class (SOC) and preferred term (PT) and a Delphi, a well- structured technique using collective consensus of multiple clinical experts [36]. Symptoms that may be associated with TEA are presented in Table 2.

Causality is assessed by evaluating the following causal factors according to the WHO-UMC criteria [37], which are the most widely used worldwide.

Is there a temporal relationship between the TEA and the occurrence of the AE?Does the same AE occur if TEA is repeated?Is it possible that the patient’s underlying medical condition or concomitant medication or procedure is the cause?Has the same AE been reported in the past?Did the AE improve after TEA was stopped?Is there a reasonable biological relationship between the procedure and the AE?

The outcome measure is the incidence, nature, and severity of AEs associated with TEA. During the 3-month post-treatment period, the incidence of AEs and rate of TEA treatment discontinuation due to AEs will be assessed. In addition, patient-, practitioner-, and intervention-related factors associated with the occurrence of AEs will be examined. The Standard Protocol Items: Recommendations for Interventional Trials (SPIRIT) schedule of enrollment, interventions, and assessments is shown in Table 1. The SPIRIT Checklist can be found in the Supplementary Files.

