#### 2.4.4. Data Collection and Management

Trial staff will create a safety information report for each AE that occurs after TEA treatment. To ensure inter-rater standardization, trial staff were trained in a 1-day workshop on consistent assessment criteria, protocols, and reporting forms. The training included case scenarios, role-playing, and practical exercises, followed by performance assessments and feedback. Ongoing AEs at the time of the report will be verified at the next follow-up evaluation and documented until resolution. Patients will be encouraged to self-report AEs using an application. All data will be retained for three years after the study’s completion. For security, the source data will be protected using study identification numbers. Personal patient information will be stored in a subject identification log, which will be kept in a locked cabinet accessible only to authorized personnel. Protocol revisions will be managed by Sangji University Korean Medicine Hospital, the central coordinating facility. They will conduct site-level monitoring to ensure the protection of participant rights, and adherence to research protocols.

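### Repeat AEs are collapsed by preferred term with severity and causality maximised separately, so a TEA-associated term can carry the severity of an unrelated episode, and the counting of recurrences is left unclear

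*Protocol article*

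**What the plan says.** Protocol article, Section 2.5.2 (Statistical Methods), sets the tabulation rules in three consecutive sentences.

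- On counting: "The incidence and incidence rates will be presented by PT", with the qualification that "multiple occurrences of the same AE by PT in the same subject will be considered as a single event".
- On grading: "different discovered severities and causalities for the same AE will be treated as the maximum severities and causalities, respectively". The last word makes these two separate maxima.
- On a further display: "Moreover, AEs associated with TEA and SAEs will be presented as events".

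Section 2.4.3 (Outcome Measures) defines the outcome as how often AEs associated with TEA occur, what they are and how severe they are.

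Participants may have several sessions: "all additional TEA treatments after the first treatment will be collected as V2 to Vn in this study" (Section 2.1). The caption of Table 1 adds that "follow-up assessments are conducted 7 days after each additional treatment to monitor any adverse events". Table 1 also has the thread, area, insertion count and depth recorded afresh at each additional session. Data are captured per event: "Trial staff will create a safety information report for each AE that occurs after TEA treatment" (Section 2.4.4).

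**The concern.** Two things follow from reading these rules together.

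First, the outcome joins severity to causality: causality decides whether an AE counts as associated with TEA, and severity then describes it. Once episodes are merged and each attribute is maximised on its own, the causality can come from one episode and the severity from another. Take a participant with mild insertion pain judged related after the first session and a severe, unrelated pain flare some weeks later. If both are coded to one PT, the merged record is severe and TEA-associated. The setting makes this plausible. Section 2.3 lists lumbar, cervical, shoulder and knee disorders as indications and permits concurrent treatments, and Table 2 lists pain as both a local and a systemic symptom.

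Second, each session is a new exposure. The Discussion reports that pilot AEs arose most often on the day of the procedure, so bruising after a fourth session is a new event. If the single-event rule governs the incidence rates by PT, that recurrence is not counted. Its link to that session's materials and technique is also lost from the tabulation, although the study sets out to examine intervention-related factors.

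At stake is the description of severe related events, which readers of a safety study look at first, and whether the results can speak about risk per procedure.

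**Working it through.** **The plan's own figure.** Section 2.5.1 gives p = 0.12, d = 0.035, z = 1.96 and 5% dropout. Then 0.12 × 0.88 × 1.96² / 0.035² = 331.16 (printed as 331.2), and 331.16 / 0.95 = 348.6, rounded up to 349, with about 350 recruited. This reproduces. It concerns one patient-level proportion; the collapsing rule does not enter it and nothing below changes it.

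**Separate maxima.** The documents give no number of sessions and no severity or causality mix, so these are assumptions. Let a participant have m episodes of one PT, each severe with probability s and related with probability r, all independent.

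- Merged record is severe and related: C = [1 − (1 − s)^m] × [1 − (1 − r)^m]
- At least one episode is itself severe and related: T = 1 − (1 − s·r)^m
- Share of merged severe-and-related records that match no single episode: (C − T) / C

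| m | s | r | C | T | C − T | Share |
|---|---|---|---|---|---|---|
| 2 | 2% | 50% | 2.97% | 1.99% | 0.98 points | 33% |
| 2 | 5% | 50% | 7.31% | 4.94% | 2.37 points | 32% |
| 2 | 10% | 50% | 14.25% | 9.75% | 4.50 points | 32% |
| 2 | 10% | 80% | 18.24% | 15.36% | 2.88 points | 16% |
| 3 | 2% | 30% | 3.86% | 1.79% | 2.07 points | 54% |
| 4 | 10% | 50% | 32.24% | 18.55% | 13.69 points | 42% |
| 2 | 10% | 100% | 19.00% | 19.00% | 0 | 0% |

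Over m = 2 to 3, s = 2% to 10% and r = 30% to 80%, the share runs from about 16% to 54%. With m = 1, C = T = s·r and the share is zero.

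These percentages apply only to participants who have m episodes of the same PT. To turn them into counts, take the planning figure as the share of participants with any AE: 0.12 × 350 = 42, with one recurring PT each.

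- All 42 with two episodes, s = 10%, r = 50%: 42 × 0.0450 = 1.9 participants.
- Half of them: 21 × 0.0450 = 0.9.
- All 42 with two episodes, s = 2%, r = 50%: 42 × 0.0098 = 0.4.
- All 42 with four episodes, s = 10%, r = 50%: 42 × 0.1369 = 5.8. Nothing in the documents supports so many recurrences.

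**Recurrences.** Take N = 332 evaluable participants, k sessions each and an assumed per-session risk q of one PT. Occurrences are N·q·k; participants counted once are N·[1 − (1 − q)^k].

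- Independent sessions, q = 12%, k = 3: 332 × 0.12 × 3 = 119.5 occurrences against 332 × (1 − 0.88³) = 105.8 participants, so 11.5% of occurrences are not counted.
- Independent sessions, q = 2% to 12%, k = 2 to 5: 1% to 21% not counted.
- The same 12% of participants react at every session: the share not counted is 1 − 1/k, that is 50% (k = 2), 67% (k = 3) or 80% (k = 5).
- One session: nothing is lost.

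**The case against.** Counting a participant once per PT at worst severity is a common convention and is right for patient-level incidence. The sample size targets a patient-level proportion, and the bivariate comparisons are between participants with and without AEs. A maximum is also sensible for one ongoing AE that is graded again at follow-up (Section 2.4.4). All of this stands, and the fix keeps it.

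A reader might infer that the rule necessarily creates severe related events that never happened. The documents do not support that. It takes at least two episodes of one PT in a participant, with severity and relatedness falling on different episodes. No explicit severity-by-causality table is planned, and separate tables of maximum severity and maximum causality would contain no false event. What remains is that severity among TEA-associated AEs, as Section 2.4.3 words the outcome, is already a joint display. One might reply that Section 2.4.2 defines every AE by temporal association, so that the outcome selects nothing. But Section 2.5.2 sets AEs associated with TEA apart from all AEs collected, so there the term marks a subset.

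A reader might also infer that recurrences vanish from the report, or that a per-treatment rate is biased downward. The documents plan no per-treatment rate, and "Moreover, AEs associated with TEA and SAEs will be presented as events" may well mean that related recurrences are shown individually. Yet that sentence follows closely on one that has just redefined repeat occurrences as a single event, and it does not say which unit it uses. Further detail on denominators is something a condensed article can leave to the full protocol or analysis plan.

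Finally, because one of the causality questions is "Does the same AE occur if TEA is repeated", a reader might think that the collapse strips recurrence from the causality assessment. It does not. Causality is judged at the scheduled assessments in Table 1, on a report made for each AE. The PT rule acts later, at tabulation.

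On size, the Introduction and Discussion describe AEs as mostly mild and transient, which points to the lower end of the assumed severity range.

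**Conclusion.** The point holds in a limited form. As worded, Section 2.5.2 allows a PT to count as TEA-associated through one episode while carrying the severity of another, unrelated one. The likely number is small: about two participants at most if everyone with an AE had two episodes of one PT (10% severe, 50% related), and under one with fewer recurrences or milder events. It is nil with one episode or when all episodes are related. These figures assume independence and a session, severity and causality mix that the documents do not give. In a safety study of about 350, even one spurious severe related event would be noticed.

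Separately, the section leaves it unclear whether its event-level display overrides the single-event rule. If it does not, the share of occurrences left uncounted could be anything from about 1% to 80%, depending on how strongly the same participants react at repeated sessions. This is worth correcting before analysis, but it does not undermine the patient-level incidence or the sample size.

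**What to change.** Amend Section 2.5.2 in three places:

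1. For AEs associated with TEA, report the maximum severity among the episodes judged related, so that severity and causality come from the same episode. Tabulate unrelated episodes of the same PT separately.
2. State that the once-per-PT rule applies to patient-level incidence only. Keep the maximum-severity rule for successive gradings of a single ongoing AE.
3. State that the event-level presentation of TEA-associated AEs counts every recurrence, and give it over the total number of TEA sessions.

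The cost is a change of wording and one extra table. Reports for each AE, onset and resolution dates, and treatment details at every session are already collected, so no new data are needed and the sample size is unaffected.
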